### Eligibility criteria

One male and one female adult (age ≥ 18 years) in each study household will be invited to participate. The exclusion criteria are subjects known to have high serum potassium levels, are taking medications known to potentially induce hyperkalemia (potassium-sparing diuretics, Angiotensin-converting enzyme (ACE) inhibitors, Angiotensin II receptor blockers, digoxin), are already taking potassium supplements, or those who have known kidney disease at baseline. Additionally, all adults residing in the selected households initially screened for intervention will undergo serum creatinine testing, with those with estimated glomerular filtrate rate (eGFR) values < 60 ml/min/body surface area excluded from the intervention but kept in the intervention group by intention-to-treat principles to avoid breaking of randomization. Although minors will not be involved in the study, to avoid spillover injury to children in the intervention households, all members of intervention households under the age of 18 will also undergo urine dipstick testing. If proteinuria (as +  + protein on urinalysis) is detected on two separate tests spaced three days apart, the household will be excluded from receiving the LSSS intervention (but followed in the intervention arm to avoid breaking randomization).

Lastly, potential participants (but not households) will be excluded if they have (1) a terminal illness, (2) are substantially mentally disabled (and thus unable to give consent), or (3) are bedridden.

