### Relevant concomitant care permitted or prohibited during the trial

All participants will be encouraged to continue usual health care during the span of the trial. No changes should be made in their routine healthcare screening or therapy—rather, any participants found to have developed exclusion criteria medical conditions during the study will be removed from the free LSSS intervention arm.

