### Recruitment

Given concerns for lower uptake among study participants randomized to the education only arm, we decided to build a conservative estimate approximated from the lowest value of uptake in the literature of free salt substitute of 75% [31, 38]. This would support the selection of a final sample size of 206 participants per study arm, leading to a total study recruitment requirement of 618 subjects. This is well within the 2,181 subjects currently registered within the BRAC cohort described above.

We shall recruit study households in the following stages: (a) the eligible households in the sampling frame will be listed against the inclusion criteria, i.e., households without any diagnosed case of chronic kidney disease (CKD), nephrotic syndrome, or hyperkalemia, no history of current intake of potassium supplement or potassium-elevating medications, and households consisting of at least two adults (aged ≥ 18 years) willing to participate in the trial; (b) from the eligible households, we shall choose a systematic random sample (with an interval of five houses) to create buffers among study households to reduce the chances of spill-over; (c) the systematic random sample of 309 households will be further inflated by the current CKD prevalence of 17.3% in Bangladesh; the resulting 362 households will then undergo the randomization process [39]. We will plan to exclude the households with CKD or nephrotic syndrome cases; to ensure this, we will perform serum creatinine tests among the adults and urine dipstick tests among those under 18 years of age with the exclusion criteria previously enumerated.

The aforementioned recruitment areas of Uttor Basupara, Basupara, and Mondolpara are adjacent to one another and are further divided into six regions. As homes within these regions are not evenly clustered in an area (and do not adhere to a geographic grid with convenient central points of interest), we will designate one end of the area as the starting point. The field workers will use a random number generator to select the first household, then move on to enrolling homes sequentially, maintaining a gap of five households between enrolled homes. This process will be continued until the end of an area is reached.

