### Plans for collection, laboratory evaluation, and storage of biological specimens for genetic or molecular analysis in this trial/future use

Trained specialists will be recruited to collect blood specimens from adults residing in households of the salt-recipient participants. The samples will be stored by the hospital for the period of testing and destroyed once the reports are generated. Serum creatinine tests will be conducted on the collected blood samples.

Urine samples will be collected from children (under 18) residing in households of salt-recipient participants. Trained field workers will perform spot tests, and the samples will be destroyed once the results are recorded. These two tests will be conducted only once before the initiation of the intervention.

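### Recruitment excludes households with a positive renal test after 362 are randomised, while Eligibility criteria keeps them in their arm; if applied to the tested LSSS arm alone, the exclusion could bias both contrasts involving that arm

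*Protocol article*

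**What the plan says.** **What happens to affected households.** Recruitment inflates the systematic sample of 309 households by a 17.3% CKD prevalence and says that "the resulting 362 households will then undergo the randomization process". The next sentence reads "We will plan to exclude the households with CKD or nephrotic syndrome cases", to be done by creatinine tests in adults and dipsticks in those under 18. Eligibility criteria says otherwise. Adults with eGFR below 60 are "excluded from the intervention but kept in the intervention group by intention-to-treat principles to avoid breaking of randomization". For repeated proteinuria in a child, "the household will be excluded from receiving the LSSS intervention (but followed in the intervention arm to avoid breaking randomization".

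**Later cases.** The section on concomitant care says that participants who develop an exclusion condition during the study "will be removed from the free LSSS intervention arm". The retention section plans to collect outcomes from people who stop or depart from the intervention. The statistical methods and missing-data sections both state intention-to-treat analysis.

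**Who is tested, and when.** The specimen section has specialists "collect blood specimens from adults residing in households of the salt-recipient participants" and adds: "Urine samples will be collected from children (under 18) residing in households of salt-recipient participants". On timing it says: "These two tests will be conducted only once before the initiation of the intervention". The Abstract lists abnormal creatinine as a baseline exclusion. The additional consent provisions place blood and urine collection in screening. The Participant timeline puts the eligibility screen before allocation.

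**The concern.** The two rules lead to different analysed samples. Under Eligibility criteria, a positive test affects receipt of LSSS but not membership of the arm. Under Recruitment read literally, the household leaves the trial.

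This matters because testing appears to be one-sided. Salt-recipient households can be identified only once arms are assigned, and a concern about breaking randomisation makes sense only after allocation. The specimen section plans no test in control or information-only households, so no matching exclusion could be made there. Removing households from the LSSS arm alone, on a result related to renal function, would leave that arm no longer comparable with the other two. Two of the three planned comparisons involve it: control versus LSSS, and information only versus LSSS. If those removed have higher systolic pressure than those who remain, the distortion favours LSSS.

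**Working it through.** **Inputs from the protocol.** 309 households, 17.3% and 362 (Recruitment); three arms; target effect 2.0 mm Hg (Sample size); baseline BP as a covariate (Statistical methods).

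**Assumed inputs, not in the protocol.** A systolic excess D of 5, 10 or 15 mm Hg in removed households over those remaining, the same at baseline and endline. A slope b of 0.7 of endline on baseline pressure.

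**Reproducing the plan's figure.** 206 × 3 = 618 participants, and 618 / 2 = 309 households. 309 × 1.173 = 362.5, stated as 362. The figure reproduces.

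**What the inflation implies.** With equal allocation, 362 / 3 = 120.7 households per arm.
- Affected households kept and followed: all 362 remain.
- 17.3% lost from the LSSS arm only: 120.7 × 0.827 = 99.8 remain there, and 2 × 120.7 + 99.8 = 341 in total.
- 17.3% lost from all arms: 362 × 0.827 = 299 remain, below 309.

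No scenario returns 309, so the arithmetic does not reveal which rule the inflation was meant to serve.

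**Size of the distortion under one-arm exclusion.** With a share q removed, the LSSS mean shifts by −q × D unadjusted, and by −q × D × (1 − b) after adjustment for baseline. With q = 0.173:

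| D (mm Hg) | Unadjusted shift | Baseline-adjusted shift (b = 0.7) |
|---|---|---|
| 5 | −0.87 | −0.26 |
| 10 | −1.73 | −0.52 |
| 15 | −2.60 | −0.78 |

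The planned model adjusts for baseline BP, so the last column is the relevant one. Against 2.0 mm Hg it is 0.26 / 2.0 = 13% to 0.78 / 2.0 = 39% of the target.

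**The passages on timing, side by side.** The specimen section implies testing after allocation in one arm. Recruitment mentions the tests after randomisation but does not limit them to one arm. The Abstract, consent provisions and timeline imply screening before allocation. Eligibility criteria refers to adults in the selected households initially screened for creatinine, but to intervention households for dipsticks. One procedure cannot satisfy all of these.

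**The case against.** The strongest reply is that the analysis rule is already settled. Eligibility criteria keeps affected people and households in the arm, the retention section covers those who stop the intervention, and two statistical sections say intention-to-treat. No section defines an analysis set without these households. The Recruitment sentence also ends by referring back to exclusion criteria listed earlier, which may import the keep-and-follow rule. On that reading there is dilution but no bias. This reading is possible. It does not remove the need for a correction: the sentence still says that households are excluded, the sample is inflated for CKD with no other stated purpose, and an intention-to-treat statement at analysis cannot recover households that were never followed.

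Several stronger readings are tempting but not supported:
- **That testing definitely follows allocation.** This is an inference from the specimen section, from the order of Recruitment and from the wish to protect randomisation. Three other places contradict it.
- **That the concomitant-care sentence removes people from the analysis.** It can equally mean that LSSS supply ends, in line with the discontinuation section.
- **That Recruitment intends exactly 309 households to remain.** It does not say so.
- **That the spurious benefit could exceed the target.** The −2.60 figure is unadjusted and takes the largest assumed excess.
- **That far more than 17.3% of households would be lost.** If the prevalence were per adult, with two independent adults tested, the share would be 1 − 0.827² = 31.6%. The plan applies 17.3% to households and already removes diagnosed CKD beforehand, so the share newly detected by testing is likely to be below 17.3%.

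**Conclusion.** The protocol contradicts itself on whether randomised households with a positive renal test stay in the trial, and it is inconsistent on who is tested and when. Both need correcting as written. Bias is conditional: it arises only if the Recruitment exclusion is applied to the LSSS arm alone. In that case the spurious LSSS benefit would be about 0.3 to 0.8 mm Hg in the planned model (0.9 to 2.6 unadjusted), against a 2.0 mm Hg target. Those figures rest on 17.3% removed, which is upper-end, and on an assumed excess of 5 to 15 mm Hg and a slope of 0.7, neither of which the protocol gives. The direction depends on the excess being positive. A reader might infer that the primary comparison is already biased. The documents do not support that, because under the Eligibility rule this bias is zero.

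**What to change.** - In Recruitment, replace the exclusion sentence with the rule already in Eligibility criteria: every randomised household is followed and analysed in its allocated arm whatever its renal test result. Add that no analysis set is defined by a test done in one arm only.
- In the concomitant-care section, make clear that removal from the LSSS arm does not mean removal from follow-up or analysis.
- Reconcile the Abstract, Eligibility criteria, the consent provisions, the timeline, Recruitment and the specimen section on who is tested and when relative to allocation. Which screening procedure is right is for the investigators to decide.
- Restate what the inflation from 309 to 362 is for, since under the keep-and-follow rule no household is lost to a positive test.

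The cost of the follow-and-analyse rule is wording. The statistical downside is some dilution of the intention-to-treat estimate by households in the LSSS arm that do not receive LSSS, and the plan should say so. The rule needs to be fixed before follow-up ends, because outcomes not collected cannot be recovered at analysis.

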## Assignment of interventions: allocation

### Sequence generation

The allocation sequence will be generated using computer-generated random numbers. No stratification will be performed. To reduce the predictability of a random sequence, blocking will be performed via a separate document that is unavailable to the fieldworkers who enroll participants and/or assign interventions. The randomization allocation process will be performed by a separate team independent of the fieldworkers.

### Concealment mechanism

The allocation sequence will be implemented via a central telephone with the allocation sequence known only to the study team member responsible for the call in order to conceal the sequence until interventions are assigned.

### Implementation

The allocation sequence will be generated prior to study commencement by a study team member who will not be involved in the enrollment and assignment of participants to specific intervention arms. Fieldworkers trained in research methods and good clinical practice will enroll participants during a home visit. Afterwards, they will inform participants of the intervention arm they have been randomized to based on the assignment made by a non-fieldworker study team member (who will not be involved in the enrollment process).

## Assignment of interventions: blinding

### Who will be blinded

Blinding will be performed for the data analyst but not the intervention community health worker nor the participant (as it will not be possible to do so, given the nature of the intervention). Blinding will be achieved by number coding the intervention groups, with codes not shared with the analyst until the conclusion of data analysis.

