### Outcomes

The primary outcome variable of our study is systolic blood pressure (SBP) as a continuous variable.

Secondary outcome variables will include:Diastolic blood pressure (DBP)Hypertension (defined as a systolic blood pressure ≥ 140 mm Hg or diastolic blood pressure ≥ 90 mm Hg or reporting to be taking antihypertensive medication)Systolic blood pressure among adults who had hypertension at the time of the baseline surveyDiastolic blood pressure among adults who had hypertension at the time of the baseline surveyHypertension control (defined as a systolic blood pressure < 140 mm Hg and a diastolic blood pressure < 90 mm Hg) among adults who had hypertension at the time of the baseline surveySelf-reported sodium intake (as estimated using typical daily dietary recall of both added salt and processed food/high salt food products)Self-reported low-sodium salt intake (as estimated using typical daily, 1-week, and 1-month recall)

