## Statistical methods

### Statistical methods for primary and secondary outcomes

Our primary outcome, systolic blood pressure (outcome 1), will be treated as a continuous variable. It will be analyzed using linear regression to estimate the magnitude of the treatment effect of each study arm intervention. The secondary outcomes of diastolic blood pressure (outcome 2), as well as SBP and DBP among hypertensive individuals (3 and 4), will similarly be treated as continuous variables, to be summarized using linear regression. The secondary outcomes of hypertension (2) and hypertension control (5) will be assessed as a binary variable, summarized as an odds ratio (OR) using logistic regression. Lastly, self-reported sodium intake (6) and low-sodium salt intake (7) will be treated as continuous variables and analyzed using linear regression.

In the primary analysis, we will regress the outcome onto a categorical variable for the study arm (control, or intervention arms 2 and 3). We will calculate three beta coefficients with corresponding p-values to estimate the magnitude of the treatment effect of each study arm (with units in millimeters of mercury). Namely, these three study/comparisons are (i) control vs. CHW education/information only; (ii) control vs. CHW education/information + direct LSSS provision; and (iii) CHW education/information only vs. CHW education/information + direct LSSS provision. The model will include baseline BP as a covariate for adjustment. Should there be variations in other baseline characteristics between groups, we will further adjust our model for residual potential confounding sources such as age, gender, and clinical comorbidities. Secondary analyses of continuous variables will be treated similarly. In the secondary analyses of binary variables, we will similarly regress the outcome over the categorical variable for the study arm and strata to yield odds ratios estimating likelihood of the outcome.

Prespecified subgroup analyses will include sex, age over 65 years, participants hypertensive at baseline, and individuals normotensive at baseline. We will test for significance in these subgroup analyses by the use of an interaction term between the study arm and the subgroup variable.

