## Oversight and monitoring

### Composition of the coordinating center and trial steering committee

The coordinating center will be based at the BRAC James P Grant School of Public Health, BRAC University (BRAC JPGSPH). As previously noted above, BRAC JPGSPH has already worked with the target population community, with many of the potential study participants previously enrolled into research studies by the institution as part of a larger Wellcome-trust funded multinational biobank to better understand the patterns and determinants of cardiovascular health in South Asian people in a cross-sectional analysis. BRAC JPGSPH also has substantial experience working with and evaluating interventions using community health workers. The BRAC JPGSPH team involves multiple investigators with extensive experience in epidemiology, noncommunicable disease research, community health research, and clinical trials in this setting. As such, the BRAC JPSGSPH coordinating center team’s role will be as equal collaborators on the study design and primary team for the on-the-ground subject recruitment, personnel management, and trial protocol enactment. This coordinating center will also be the principal team for liaising with and disseminating the results of the study to local and national stakeholders.

These members will supervise the day-to-day operations of the present study, including:Drafting, revision, and defense of study protocols and Bangladesh-level human subjects research ethical approval protocols;Recruitment, training, equipment, and evaluation of study fieldworkers;Recruitment, training, equipment, and evaluation of study intervention community health workers;Identification, testing, and purchase of intervention LSSS product;Recruitment of study subjects;Randomization of study subjects (including generation and implementation of the randomization allocation sequence);Primary data collection, security, and integrity confirmation. This process will involve data de-identification and management as well.

BRAC JPGSPH study team members will also be involved in the entire data analysis and publication/results dissemination phase and will be primarily responsible for the dissemination of results within Bangladesh and with national stakeholders (e.g., the Ministry of Health).

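### Number-coded arms cannot keep the analyst blind to the free-salt arm, because low-sodium salt intake is itself an outcome analysed by arm

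*Protocol article*

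**What the plan says.** Under Who will be blinded, the protocol states: "Blinding will be performed for the data analyst but not the intervention community health worker nor the participant". The mechanism follows: "Blinding will be achieved by number coding the intervention groups, with codes not shared with the analyst until the conclusion of data analysis". No other role is said to be masked. Under Implementation, fieldworkers enrol participants and afterwards "they will inform participants of the intervention arm they have been randomized to". Fieldworkers also take the blood pressure readings (Plans for assessment and collection of outcomes).

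The last secondary outcome in the Outcomes section is "Self-reported low-sodium salt intake (as estimated using typical daily, 1-week, and 1-month recall"). The statistical methods section plans its analysis: "Lastly, self-reported sodium intake (6) and low-sodium salt intake (7) will be treated as continuous variables and analyzed using linear regression". It adds that continuous secondary outcomes are handled like the primary one, that is, regressed on a categorical variable for arm. Intervention description gives LSSS to one arm only.

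On covariates, the same section fixes baseline blood pressure and then says: "Should there be variations in other baseline characteristics between groups, we will further adjust our model". Age, gender and comorbidities are given as examples.

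**The concern.** A numeric code hides an arm only while nothing in the data shows which treatment that arm received. Outcome 7 measures use of the product that one arm is given. The protocol promises a blind that lasts to the end of an analysis whose own content reveals one of the three codes. It sets no order of analyses that would postpone this.

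At stake is the discretion that an analyst blind exists to protect. Extra covariates are added if baseline characteristics vary between groups. No criterion for such variation is given, and the list of candidates is open. If those choices are made after the free-salt code is known, they can drift towards the hypothesis, and the trial report would still describe the analysis as blinded. Because the analyst is the only person stated to be blinded, no other masking stands behind this one.

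**Working it through.** The plan gives no figure on this point to reproduce. The check sets the sections side by side and adds one calculation, to see whether some LSSS use in the other arms could hide the free-salt code.

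**Step 1: does the analyst have to see outcome 7 by code?** Yes, on the stated plan. It is a listed secondary outcome with a stated regression on arm, and the codes are withheld until data analysis concludes. The article mentions one data analyst and no separate person or later stage for outcome 7.

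**Step 2: would use in the other arms blur the picture?** Provisions for post-trial care describes LSSS as sold in nearby countries, and the Discussion mentions open-market purchase. Intake elsewhere may therefore be above zero.

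Inputs:
- Households per arm: 309 / 3 = 103 (Abstract and Recruitment).
- Uptake *u* where LSSS is supplied: 74.3% to 94.1% in prior trials (Sample size), and the 75% used under Recruitment.
- Use *q* in each of the other two arms: not given in the documents. Assumed range: 0%, 5%, 10%, 20% and 30%.

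The probability that the free-salt code has strictly the most LSSS-using households is

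P = Σₓ Bin(x; 103, *u*) × [F(x − 1; 103, *q*)]²,

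where F is the binomial distribution function. The separation in standard errors is

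z = (*u* − *q*) / √{[*u*(1 − *u*) + *q*(1 − *q*)] / 103}.

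| *u* | *q* | P | z |
|---|---|---|---|
| 0.743 | 0 | 1.000 | 17.3 |
| 0.743 | 0.30 | 1.000 | 7.1 |
| 0.75 | 0 | 1.000 | 17.6 |
| 0.75 | 0.30 | 1.000 | 7.2 |
| 0.941 | 0 | 1.000 | 40.5 |
| 0.941 | 0.30 | 1.000 | 12.6 |

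For the least favourable row, z = 0.443 / √[(0.1910 + 0.2100) / 103] = 0.443 / 0.0624 = 7.1. In all 15 combinations of *u* and *q*, P rounds to 1 at six decimals. Counted in people at 75% uptake, about 0.75 × 206 = 154.5 participants under one code would report LSSS use.

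**Step 3: how much of the blind is lost?** The three primary comparisons are control versus education, control versus education plus LSSS, and education versus education plus LSSS. The identified arm is in the last two. Outcome 7 does not separate control from education, so that comparison can stay masked.

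**Step 4: what is still open when the code is exposed?** The choice of extra covariates is open. Whether to impute is not, because the missing-data section fixes it by a 5% threshold. Only the content of the imputation model remains to be settled.

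**The case against.** The strongest reply is that this is a narrow point about sequencing. Revealing one code of three is common in open-label trials with an uptake outcome. The endpoint is an automated-cuff reading analysed by intention to treat with a stated regression. No bias in systolic pressure has been shown, and prespecifying the covariates would remove the main discretion under any blinding. All of that stands, and it limits how serious the point is. It does not remove the conflict between the stated duration of the blind and the stated outcome. Nor does an unseen analysis plan settle it, because the article itself fixes the mechanism and its end point.

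A reader might also infer more than the documents support:

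- **That someone analysing the data holds the allocation key.** The coordinating centre generates and implements the sequence, and "BRAC JPGSPH study team members will also be involved in the entire data analysis". That is overlap at team level only. Concealment mechanism limits knowledge of the sequence to the team member who takes the call. The primary analysis is assigned to the other university's team, and Data Availability limits two authors to a de-identified, coded dataset during the study period.
- **That compliance and laboratory variables unmask the analyst too.** Unused LSSS is measured monthly, and blood results enter the trial database, but nothing places either in the analyst's file.
- **That renal tests exist only in the salt arm.** One section plans to "collect blood specimens from adults residing in households of the salt-recipient participants". Eligibility criteria and Recruitment can be read as testing more widely.
- **That the analyst may decide whether to impute.** The 5% rule decides that.
- **That the whole blind collapses.** Control versus education can remain masked.

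**Conclusion.** The point holds in a limited form. As written, number coding cannot keep the analyst blind to the free-salt arm until analysis ends, because outcome 7 identifies that arm at the first tabulation. Identification is practically certain across the uptake range the protocol cites, even with an assumed 30% use in each other arm. Two of the three primary comparisons are affected.

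This rests on three assumptions: the same analyst handles outcome 7 and the blood pressure outcomes, household use of LSSS is close to the cited uptake, and use elsewhere does not exceed the assumed range. The consequence is an analysis that could be reported as blinded when it was not, with covariate choice still open. The size of any resulting bias in blood pressure is not known and is not claimed. The change is worth making because it is cheap and lets the protocol's own statement hold.

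**What to change.** Amend Who will be blinded to provide for release in two steps.

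1. The analyst first receives a coded file with household, baseline covariates, baseline and endline blood pressure, and antihypertensive use. It contains no LSSS intake and no unused-LSSS or renal-screening variables. It also omits endline sodium recall (outcome 6), because both interventions aim to change it and it may hint at arm. On this file the analyst fixes the covariates and the imputation model, then locks the systolic, diastolic and hypertension analyses.
2. Outcomes 6 and 7 and the compliance data are released only after that lock.

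Also state that the individual who holds the allocation sequence takes no part in analysis decisions before the lock.

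The cost is a short wording change and a split data export, with no new data or staff. Outcomes 6 and 7 and the compliance analyses wait until the blood pressure analyses are locked, and the variables held back cannot serve as auxiliary variables in the locked imputation model.
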